## Abstract

**Background:**

Chronic subdural hematoma is a persistent, bloody to serous fluid retention in the subdural space between the dura mater and arachnoid mater, usually caused by an initial trauma, and is one of the most common traumatic intracranial hemorrhages in western industrialized nations. In the event of a compressive effect on the brain, the hematoma is usually relieved by means of a burr hole trephination. In view of the high postoperative recurrence rate, conservative treatment methods have been investigated both as a competitor to surgery alone in cases where the indication for surgery is debatable and as a supportive therapy for surgical hematoma relief. Studies on embolization of the middle meningeal artery during surgery as well as studies on postoperative drug therapy using tranexamic acid have shown the most promise. However, there is currently a lack of studies that randomly compare the effectiveness of these two perioperative treatment strategies regarding to their efficacy in avoiding revision surgery and the safety of the respective procedure.

**Methods:**

TABASCO is a prospective, randomized, two-arm, multicenter, clinical trial designed to determine whether postoperative treatment of chronic subdural hematomas using adjuvant drug therapy with tranexamic acid (test group) is equivalent to postoperative embolization of the arteria meningea media (control group) in terms of postoperative volume reduction of the hematoma and the need for revision surgery of CSDH. Patients over 18 years of age who have undergone surgery for CSDH for the first time no more than 24 h before inclusion in the study will be randomized 1:1 to the test group or control group. The primary endpoint is the postoperative volume decrease of a primarily surgically relieved CSDH quantitatively and regarding to the time course on the affected side in a study period of 3 months postoperatively. The secondary endpoint of this study is to investigate the extent to which the rate of necessary revision surgery can be influenced by the adjuvant therapy procedures over the course of 3 months. The tertiary endpoint is the neurological outcome of the patients included in the study and assigned to the different treatment arms after a total follow-up period of 3 months as well as the complication rate of the adjuvant procedures used. Assuming a risk difference of 8% for rebleeding and surgical revision, with an applied power of 80%, 276 patients (138 per group) will be included in this study.

**Discussion:**

The TABASCO study will provide clinical evidence as to whether embolization of the middle meningeal artery in addition to surgery is comparable to postoperative drug therapy using tranexamic acid as an adjuvant treatment method for operated chronic subdural hematomas in terms of hematoma volume reduction, revision rate and safety of the procedures.

**Trial registration:**

German Clinical Trials Registry (Deutsches Register Klinischer Studien (DRKS)) DRKS00033515. Registered on 05 Feb 2024.

**Supplementary Information:**

The online version contains supplementary material available at 10.1186/s13063-025-08888-6.

## Introduction

### Background and rationale {6a}

Chronic subdural hematoma (CSDH) is a persistent, bloody to serous fluid retention in the subdural space between the dura mater and arachnoid mater, usually caused by an initial trauma, and is one of the most common traumatic intracranial hemorrhages in western industrialized nations [23]. The incidence rate is described between 1.7 and 20.6 per 100,000 inhabitants, whereby there is a clear age dependency. The incidence rises with increasing age and the demographic change with an elderly population as a whole on the other hand [6]. In this context, Finnish studies have shown a doubling of the incidence from 8.2 to 17.6 per 100,000 inhabitants over the last 25 years [17].

The pathophysiology leading to the development of CSDH is yet not fully understood. Originally, it was assumed that initial traumatic bleeding was caused by tears in the intracranial bridging veins, which led to additional fluid absorption in the subdural space through osmosis and thus to liquefaction and progression in size of the hematoma. However, current studies show a much more complicated pathogenesis. In contrast to acute SDH, which is caused by the rupture of bridging veins or cortical vessels, the cause of CSDH also lies in injury to the so-called dural border cell layer. This is located between the dura mater and the arachnoid mater and consists of a group of highly specialized connective tissue cells. If these cells are injured, local inflammatory reactions are set in motion. They lead to increased fibrinolysis and angiogenesis, through which the renewed healing of this layer is sought. As part of this process, an inner and outer membrane are formed. The inner membrane consists of collagen and fibroblasts and lies against the arachnoid, while the outer membrane merges into the dura mater. It contains various cells and mediators that maintain the inflammatory process. Within this framework, not only the membranes continuously are formed, but membrane septa can also develop within the CSDH. In addition, new (pathological) capillaries are formed, which have very thin walls. The fragile capillaries within the outer membrane rupture easily, which leads to renewed microbleeds into the interior of the membrane, while at the same time the plasminogen-activated hyperfibrinolysis of the membrane contents as part of the acute phase reaction leads to the prevention of regular clot formation, which in turn promotes persistent microbleeds [8]. The bleeding again stimulates the inflammatory reaction and a vicious circle of cell proliferation, angiogenesis, hyperfibrinolysis and bleeding through rupture of newly formed vessels develops [3, 17, 20]. This leads to a continuous progression of the hematoma size.

The gradual increase in volume of the hematoma can lead to displacement or a compressive effect on the adjacent brain tissue and thus to the development of neurological symptoms with the development of headaches, central motor deficits, epileptic seizures and reduced vigilance and even coma.

Where narrow, asymptomatic, chronic subdural hematomas can still be treated conservatively as part of a wait and watch or wait and scan strategy [17] with regular imaging follow-up and the interruption of any additional antiplatelet or anticoagulant therapy, hematomas with a proven compressive effect from a thickness of around 10 mm and a midline displacement of 7 mm [17] and the associated clinical symptoms must be surgically relieved.

Various techniques can be used (depending on the localization, the imaging of the CSDH and the space-occupying effect). These include burr hole trepanation as well as smaller and larger craniotomies, irrigation of the hematoma cavity and placement of a subdural drainage system [13]. Regardless of the type of surgery performed, however, a relatively high recurrence rate of 2.3–38.7% has been shown with the need for revision surgery [15, 18].

In view of the high postoperative recurrence rate, conservative treatment methods have been investigated both as a competitor to surgery alone in cases where the indication for surgery is debatable [17] and as a supportive therapy for surgical hematoma relief. Studies on embolization of the middle meningeal artery (MMA) [21] during surgery as well as studies on postoperative drug therapy using tranexamic acid were the most promising.

It was shown that postoperative drug therapy with tranexamic acid, which is a specific antifibrinolytic drug that inactivates plasminogen and thus inhibits hyperfibrinolysis [12] in order to prevent a renewed increase in the size of the CSDH by preventing microbleeds, reduced the recurrence rate and thus also the re-operation rate compared to surgical treatment of CSDH alone [2, 6, 10, 13, 14, 24, 25, 28]. In addition, several studies have shown that interventional embolization of the arteria meningea media, which is known to supply the dura mater arterially, and thus the occlusion of distal microvessels of this vessel also reduces the active processes of cell proliferation, angiogenesis and secretion, which cause the recurrence of CSDH [1, 7, 16, 19, 22].

However, there is currently a lack of studies that randomly compare the effectiveness of these two perioperative treatment strategies regarding to their efficacy in avoiding revision surgery and the safety of the respective procedure.

### Objectives {7}

#### Primary objective

The primary aim of this study is to investigate how the postoperative volume decrease of a primarily surgically relieved CSDH can be influenced quantitatively and regarding to the time course by a postoperative adjuvant drug therapy with tranexamic acid in comparison to a postoperative interventional embolization of the MMA on the affected side in a study period of 3 months postoperatively.

#### Secondary objective

The secondary objective of this study is to investigate to what extent the rate of necessary revision interventions of a primarily surgically relieved CSDH can be influenced by postoperative adjuvant drug therapy with tranexamic acid compared to postoperative interventional embolization of the middle meningeal artery on the affected side over the course of 3 months postoperatively.

#### Tertiary objectives

The tertiary objective of this study is the presentation and evaluation of.The constellation of findings that led to the indication for revision surgery in patients included in the study,The neurological outcome of the patients included in the study and assigned to the different treatment arms after a total follow-up period of 3 months,Complications related to the interventional procedure used, andComplications and side effects due to the use of tranexamic acid.

### Trial design {8}

TABASCO is an investigator-initiated, multi-center, randomized controlled trial testing whether postoperative treatment of chronic subdural hematomas using adjuvant drug therapy with tranexamic acid (test group) is equivalent to postoperative embolization of the MMA (control group) in terms of postoperative volume reduction of the hematoma and the need for revision surgery of CSDH within a follow-up period of 3 months. Eligible patients will be allocated in a 1:1 ratio to either the test or control group.

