### Sample size {14}

In order to estimate the required sample size, the volume change of a primary operated CSDH under the adjuvant therapy forms to be investigated is analogized with the recurrence rates of primary operated and adjuvant embolized or adjuvant drug-treated CSDH in the literature with regard to the target value defined within the primary objective. For example, the MEMBRANE study, which is currently being recruited, assumes a recurrence rate of 10% when combined surgical and interventional therapy is used [11]. In comparison, the work of Hibahashi et al. [27] puts the recurrence rate of CSDH treated with a combination of surgery and medication at around 2%. Based on this, using the *z*-test for independent samples and an error of the first kind (*α* = 0.05), a sample size of 276 patients (138 per group) is required to achieve a power > 0.8 to detect a difference of 8%.

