## Statistical methods

### Statistical methods for primary and secondary outcomes {20a}

The baseline data and outcome parameters are subjected to a simple descriptive data analysis (median, minimum, maximum and standard deviation in each case; mean only for metrically scaled characteristics).

For difference tests for nominal variables (gender, use of anticoagulation prior to surgery, occurrence of complications due to adjuvant therapy procedures, need for revision surgery), the Pearson chi-squared test is used.

For difference tests of ordinally scaled measured variables (NIHSS, mRS) within the respective groups at different points in time (linked samples), the data collected is tested for normal distribution using the Shapiro–Wilk test. In the case of a parametric distribution, the *t*-test is used for linked samples. In the case of a non-parametric distribution, the Wilcoxon test is used for connected samples (for two-group tests).

For the bivariate dependency analysis of the ordinal scaled characteristics between the two groups at the same point in time, the *t*-test for unconnected samples is used for a parametric distribution and the Mann–Whitney *U*-test for a non-parametric distribution after applying the Shapiro–Wilk test.

For metric variables (hematoma volume), which are subject to a normal distribution, the *t*-test for dependent samples is used to analyze the respective groups at different points in time. In the case of a non-parametric distribution, the Wilcox sign-rank test is used for the analysis.

For the bivariate dependency analysis of the metric characteristics between the two groups at the same point in time, after applying the Shapiro–Wilk test, the *t*-test for unrelated samples is used for a parametric distribution and the Mann–Whitney *U*-test for a non-parametric distribution.

In addition, a logistic regression is tested with the revision rate as the dependent variable and the treatment groups and baseline data as independent variables.

Furthermore, a correlation analysis of the relationship between the postoperative volume size and the revision rate as well as the postoperative neurological assessment and the revision rate is performed, in each case for mixed scaling pairs with the chi-squared test. The respective singular correlation analysis is followed by an analysis of the existence of a partial correlation between the two parameters in relation to the revision rate.

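### The article states an equivalence question, but its sample size and all between-arm tests are built to detect a difference, so a non-significant result could be misread as equivalence

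*Protocol article*

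**What the plan says.** The article poses the question in two ways.

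- **Equivalence.** Trial design {8} has the trial testing whether TXA "is equivalent to postoperative embolization of the MMA (control group) in terms of postoperative volume reduction of the hematoma" and on need for revision surgery. The Abstract (Methods) says the same: TXA "is equivalent to postoperative embolization of the arteria meningea media (control group) in terms of postoperative volume reduction of the hematoma". The Abstract (Discussion) promises evidence on whether embolization "is comparable to postoperative drug therapy using tranexamic acid".
- **Neutral comparison.** The primary and secondary objectives in Objectives {7} ask how volume decrease, and to what extent the revision rate, can be influenced by one adjuvant compared with the other. Equivalence is not mentioned there.

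The quantitative sections all follow a difference comparison.

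- Sample size {14} uses a z-test for independent samples at alpha 0.05, with recurrence of 10% (surgery plus embolization) and about 2% (surgery plus drug). It arrives at 276 patients "to detect a difference of 8" percent.
- Statistical methods {20a} assigns revision surgery to the Pearson chi-squared test, introduced by "For difference tests for nominal variables". Volume gets the unpaired t-test or the Mann-Whitney U-test at each time point. A logistic regression on revision is added. The significance level is p < 0.05 throughout.
- Interim analyses {21b} also argues in terms of reaching a significant difference.

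**The concern.** The null hypothesis of a chi-squared, t- or Mann-Whitney test is that the arms do not differ. Failing to reject it is not evidence that they are alike, because a small or noisy trial fails to reject as well. Rejecting it does not settle equivalence either, since a significant difference can be too small to matter. An equivalence claim needs a stated largest acceptable difference and a confidence interval, or two one-sided tests (TOST), that rules out anything larger.

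The article asks the equivalence question and then fixes the sample size, tests and significance level for the other one. The risk lies in the main conclusion. If the tests come out non-significant, the only text on equivalence is the stated aim, and a reader could take the result as showing that the two adjuvants are interchangeable while a relevant difference in revision surgery remains possible.

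**Working it through.** **Inputs.** Recurrence 10% and 2%, alpha 0.05, power 0.8 and 138 per arm (Sample size {14}); 1:1 allocation (Trial design {8}). Sidedness is not stated. The recurrence rates are treated below as revision rates, in line with the Abstract, which describes the 8% as a risk difference for rebleeding and surgical revision.

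**1. Reproduce 276.** Pooled two-sided z-test, with mean rate 0.06:

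n = [1.960 × √(2 × 0.06 × 0.94) + 0.842 × √(0.10 × 0.90 + 0.02 × 0.98)]² / 0.08²
= [0.658 + 0.279]² / 0.0064 ≈ 137.2, so 138 per arm and 276 in total.

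This matches exactly; a one-sided test would give 108 per arm. Power at 138 per arm is Φ[(0.08 × √138 − 0.658) / 0.331] = Φ(0.850) = 0.802. So 276 comes from a two-sided difference calculation that assumes the arms differ by 8 points.

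**2. Chance of p > 0.05 at 138 per arm** (one minus the power from the same formula):

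| True rates | Chance of p > 0.05 | Source of rates |
|---|---|---|
| 10% v 2% | 20% | planning rates |
| 10% v 4% | 50% | 4% assumed |
| 10% v 5% | 65% | 5% assumed |

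**3. What a non-significant result could look like.** Take 14/138 (10.1%) v 6/138 (4.3%), a difference of 5.8 points.

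- Test: pooled rate 20/276 = 0.0725; SE = √(0.0725 × 0.9275 × 2/138) = 0.0312; z = 0.0580/0.0312 = 1.86; p = 0.063.
- Interval: unpooled SE = 0.0310; 95% CI = 5.8 ± 1.96 × 3.10 = -0.3 to 11.9 points.

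The result is non-significant, yet the interval contains 8 points and extends well beyond it.

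**4. What 276 patients would give for equivalence on revision.** The article gives no margin, so ±8 points is an assumption for illustration. With equal true rates p in both arms, SE = √(2p(1−p)/138) and TOST power (90% CI inside the margin) = 2Φ(0.08/SE − 1.645) − 1.

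| Common rate (assumed) | SE | Power, 138 per arm | n per arm for 80% power |
|---|---|---|---|
| 2% | 0.0169 | 99.8% | 53 |
| 6% | 0.0286 | 75% | 151 |
| 10% | 0.0361 | 43% | 241 |

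The 2% row is a rough approximation, since it rests on about 3 events per arm (0.02 × 138 = 2.8). If a 95% CI had to lie inside the margin, the three powers would be 99.5%, 60% and 20%.

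**5. Volume, the primary outcome.** No standard deviation and no margin in ml are given, so no corresponding figure can be worked out.

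**The case against.** The best defence is that this is in substance a difference trial. The objectives are neutral, the sample size and tests agree with each other, the interim-analysis section speaks of a significant difference, and the main Discussion describes a comparison of influence. On that reading, equivalence is loose wording in a few sentences, and the Abstract's use of comparable is ordinary language. Much of this stands. It is why the simple repair is a change of wording, with 276 and the tests left as they are. It does not remove the conflict, because Trial design {8} is where the hypothesis is stated, and it states equivalence.

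A second defence is that the article condenses a full protocol (version 2.1) that is not shown, and a margin may be given there or in an analysis plan. That is fair, so the absence of a margin is not itself the point. The point is that the visible sample size and tests are fixed for a different question from the visible aim.

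Four stronger readings are tempting and are not supported:

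- A reader might infer that the investigators will declare equivalence if p > 0.05. No section states such a rule; the text only leaves room for the misreading.
- A reader might infer that 276 patients could never support equivalence. That depends on the margin and the event rate: with ±8 points and 2% in both arms, power is about 99.8%.
- A reader might compute TOST power at the planning rates with a ±8 margin, find 5%, and treat it as evidence against the design. It follows by construction, because the margin was set equal to the planning difference.
- A reader might infer that crossover and missing data must push toward no difference. Permitted crossover tends to dilute a true difference, but missing data in an unblinded trial can bias either way.

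**Conclusion.** The concern holds as a contradiction within the article. Trial design {8} and the Abstract state an equivalence question; Sample size {14} and Statistical methods {20a} fix an analysis that can show a difference but cannot show equivalence; and Objectives {7} sides with neither.

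For revision surgery, a non-significant result has a probability of about 20% even if the planning difference of 8 points is real, and about 65% under an assumed 10% v 5%. Such a result can be compatible with a difference larger than 8 points. Whether 276 patients would suffice for an equivalence claim cannot be decided from the article: under the assumed ±8 margin, power runs from about 99.8% to 43% as the common rate goes from 2% to 10%. The margin and the common rates are assumptions, and the calculations use normal approximations. Nothing can be quantified for volume.

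**What to change.** **Preferred repair.**

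- In Trial design {8} and the Abstract (Methods), and for consistency in the Abstract (Discussion), replace the equivalence wording with a two-sided comparison of TXA and embolization. This matches Objectives {7}, Sample size {14} and Statistical methods {20a}.
- Report each between-arm difference with its 95% CI, in ml for volume and in percentage points for revision.
- State that p > 0.05 will not be taken as evidence of equivalence.

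The cost is wording only: no extra patients, procedures or change of tests. The allowed conclusion becomes more modest. The change would go through the amendment route described in section {25}; whether the registry entry also carries the equivalence wording cannot be seen from the article.

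**If equivalence is to be kept.**

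- Justify a margin in ml and one in percentage points before any comparative look at the data.
- Conclude equivalence only if the confidence interval, at a level fixed in advance, lies inside the margin.
- State the power that 276 patients give. It may be below 80%: with an assumed ±8 points and common rates of 6% to 10%, 151 to 241 per arm would be needed against the planned 138.

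This route costs more and may need more patients. Recruitment has begun and no interim analysis is planned, so either repair can still be made before outcomes are compared.

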## Methods: participants, interventions, and outcomes

### Study setting {9}

In all participating centers, after diagnostic confirmation of a unilateral chronic subdural hematoma and an associated indication for surgical relief of the hematoma, it is checked within 24 h after surgery whether they are eligible for participation in the study. Screening for inclusion in the study is carried out. After informed consent has been obtained, the patient is randomly assigned to either the test or the trial group. With randomization to the test group, adjuvant drug therapy with tranexamic acid is started. If assigned to the control group, embolization of the middle meningeal artery on the diseased side will be performed within 72 h postoperatively. The study participants are monitored according to the follow-up schedule (Table 1). All clinical investigators in all participating centers have renowned expertise in neurosurgery, neuroradiology, and endovascular interventions. Structural and process quality in terms of state-of-the-art radiological imaging, surgery, critical care, and management of complications are provided.

